We suspect that the combination of AIH and gait training leads to an additive therapeutic effect to produce greater walking recovery improvements than either alone. Prior studies show that combinatorial therapies are effective at amplifying the effects of single treatments in persons with SCI [12, 13]. Whereas combined cellular therapies are sometimes successful in rodent iSCI models, such therapies have seldom been combined with motor training in humans due to risks of systemic drug administration [14–16]. AIH is a non-invasive treatment that may serve as a ‘primer’ for SCI rehabilitation. Traditional training therapies often require more than 4 weeks for only modest long-term benefits on function. Thus, there is considerable need for more effective approaches. Repetitive AIH may fill that need and accelerate the impact of more traditional rehabilitation strategies. While past results support this exciting possibility in persons with *chronic* SCI [10, 11], we do not yet know if daily AIH alone or when combined with walking practice has a synergistic effect on improving walking function in persons at earlier stage injuries or with less initial walking ability.

There is tremendous potential for AIH to improve locomotor function via triggering or aiding rapid forms of endogenous plasticity within residual spinal circuitry after SCI [2, 17]. Prior studies have demonstrated how the greatest locomotor recovery occurred in rats with the greatest tissue sparing (> 40%) after spinal cord contusion [18, 19]. However, Basso et al. found that only a relatively small percentage of sparing (< 2%) is sufficient to trigger neural reorganization below the spinal cord injury site to achieve functionally meaningful gains [19]. Spinal plasticity peaks within the first year after injury and thus, offers a window of opportunity for early AIH treatments to help direct neural reorganization in functionally meaningful ways [20–22].

Here, we detail the study protocol of a randomized clinical trial that examines the distinct influences of repetitive exposures (daily) to AIH, with and without walking practice, on overground walking ability in persons with subacute SCI. Using an established AIH protocol known to elicit short-term improvement of walking ability in persons with chronic spinal injuries [10], we plan to examine the potential for an extended AIH protocol to elicit safe and persistent improvements in walking ability.

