### Sample size

We plan to study the effects of daily AIH alone and with WALK in N = 85 persons with subacute SCI. The sample size is a sum of participants who enroll in Aims 1 and 2. We established a Consolidated Standard of Reporting Trials CONSORT flow diagram to summarize our trial enrollment, intervention, allocation, follow-up, and analyses [24].

For Aim 1, our sample size computation focused on interventions: daily AIH versus daily SHAM. Data from our previous randomized clinical trial that examined the effects of daily AIH (vs daily SHAM) on walking speed in persons with chronic SCI showed an effect size of 0.84 at our final follow-up. Using this value, our estimated sample size for this aim is N = 34 participants (includes 12% attrition rate), for a sensitive non-parametric comparison of means between interventions to detect a significant difference at power > 0.8 (f = 0.6, F_1,39_ = 4.6; ρ = 0.4, α = .05).

For Aim 2, our sample size computation focused on interventions: daily AIH + WALK versus daily SHAM+WALK. Data from our previous randomized clinical trial that examined the effects of daily AIH + WALK (vs daily SHAM+WALK) on walking endurance (6MWT) in persons with chronic SCI showed a significant increase of total distance walked (131 ± 100 m). Our preliminary data of the effects of daily AIH alone showed an increase of 23.9 ± 18.0 m on the 6MWT. Using these values and under the hypothesis of an additive effect of daily AIH + WALK (vs daily SHAM+WALK, WALK), we anticipate the difference in change of walking distance between daily AIH + WALK vs daily SHAM+WALK or vs WALK will be approximately 100 m. Hence, our estimated sample size for this aim is N = 51 participants (includes 12% attrition rate), for a sensitive repeated measures ANOVA comparing interventions across 3 time points, using a pooled standard deviation of 90 m, to detect a significant difference at power > 0.8 (f = 0.6, F_1,38_ = 4.4; ρ = 0.4, α = .05).

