#### Randomization and stratification

We stratify eligible participants into either an ambulatory or a non-ambulatory group based on their initial walking function. The ambulatory group includes eligible participants who successfully complete one of the following without human assistance: TUG, 10MWT, or 6MWT without human assistance. Participants enrolled in the non-ambulatory group are unable to complete any of these assessments at initial screening. Prior to enrollment of the first study participant, a research statistician generated the balanced, randomization scheme for treatment allocation in both non-ambulatory and ambulatory groups using the R Statistical Package [29]. Using this scheme, the clinical coordinator assigns each participant to their respective treatment group using their alphanumeric identifier.

Although we inform participants about their group, we blind them to the treatment they receive (i.e. daily AIH or daily SHAM). The clinical raters, trainers, and data analysts are also unaware of the treatment that each participant receives during after the trial. We plan to rigorously quantify our blinding methods. Participants guess the breathing intervention received at the end of each treatment day and indicate guess confidence using a Likert scale [30, 31]. Using a contingency table and Fischer’s Exact Test, we will determine if the probability of correct guessing is different from chance. Using multivariate logistic regressions, we also will assess factors that may influence guessing (e.g., adverse events, perceived effects, and sensorimotor changes).

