### Statistical analysis

To advance our understanding and the applicability of daily AIH-induced walking recovery, we plan to test three sub-hypotheses using parametric and non-parametric statistical inferencing. Statistical significance corresponds to a p-value less than 0.05.

#### Hypothesis 1

Daily AIH improves walking recovery in persons with subacute SCI initially unable to walk as compared to daily SHAM. We plan to quantify the success of completing walking skills using our primary outcome measures (i.e., TUG, 10MWT, and 6MWT) by a recovery score of 0–3. We predict that the number of walking skills recovered will be greater for participants receiving daily AIH vs daily SHAM, indicating improved walking ability. We will use a Friedman two-way (factor 1 = intervention: daily AIH, daily SHAM; factor 2 = time: baseline, mid-test, post-test, and follow-ups) repeated measures analysis of variance (ANOVA) by ranks to compare walking recovery between and within groups. If there are significant differences, we plan post-hoc tests for pairwise comparisons [50]. We also anticipate that improvement in walking recovery will correlate with improved SCI-FAI, WISCI and LEMS scores, suggesting clinical relevance of daily AIH as an intervention across various SCI impairment levels.

#### Hypothesis 2

Daily AIH + WALK improves walking ability in ambulatory persons with subacute SCI as compared to daily SHAM+WALK and WALK. We predict a decrease in 10MWT and TUG time and an increase in 6MWT distance relative to baseline following dAIH+WALK (vs. dSHAM+WALK, WALK). We will test three related sub-hypotheses using a linear mixed model with fixed effects [51]. We will use intervention (daily AIH + WALK, daily SHAM+WALK, WALK) and time (day) as the fixed main effects, with subject as random effect, while scores for TUG (time), 10MWT (time), and 6MWT (distance) will be considered as repeated measures. Differences from baseline scores will be compared between and within interventions at mid-test, post-test, and follow-ups. If ANOVAs reveal significant differences, we will use the Tukey-Kramer post-hoc test to identify pairwise differences. If baseline measures are significantly different between intervention groups, we plan to use an analysis of co-variance (ANCOVA) to analyze these data.

#### Hypothesis 3

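### The Aim 1 rank analysis gives no proper between-arm test and cannot take a covariate; a pre-specified between-arm model adjusted for baseline strength would do both, with a power gain that depends on an unknown correlation

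*Protocol article*

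**What the plan says.** All references are to the protocol article.

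- **Analysis (Statistical analysis, Hypothesis 1).** Each walking test is given a 0-3 recovery score. The arms are to be compared by a Friedman two-way "repeated measures analysis of variance (ANOVA) by ranks to compare walking recovery between and within groups". The factors are intervention (AIH, SHAM) and time, and baseline is one of the time levels. No covariate is named. ANCOVA appears only under Hypothesis 2, and only if baselines differ significantly.
- **Entry (Randomization and stratification).** "Participants enrolled in the non-ambulatory group are unable to complete any of these assessments at initial screening".
- **Strength.** The physical screen, described with the informed consent process, includes strength among its standardized assessments. Hypothesis 1 expects that "improvement in walking recovery will correlate with improved SCI-FAI, WISCI and LEMS scores", so LEMS serves only as a correlate of improvement.
- **Size (Sample size).** "our estimated sample size for this aim is N = 34 participants (includes 12% attrition rate"). The effect comes from an earlier trial that, "on walking speed in persons with chronic SCI showed an effect size of 0.84 at our final follow-up". The calculation is described as a non-parametric comparison between interventions, "to detect a significant difference at power > 0.8 (f = 0.6, F_1,39_ = 4.6; ρ = 0.4, α = .05").

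**The concern.** The question in Aim 1 is whether AIH does better than SHAM in two independent groups. The test named for it works within participants, so the stated method and the stated question do not match.

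The method also leaves unused the baseline information most likely to predict recovery. The outcome's own baseline is compressed by the entry rule. Non-walkers may still differ widely in residual strength, and the article's Background links recovery to spared tissue, in animals ("the greatest locomotor recovery occurred in rats with the greatest tissue sparing"). Stratification is by walking ability alone, and recruitment is to be balanced on age, gender and race, so no described safeguard covers strength. With about 15 evaluable participants per arm, precision in the main Aim 1 comparison is at stake, and so is whether that comparison is defined at all.

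**Working it through.** **1. Why the named test does not compare the arms.** A Friedman test ranks the k visits within each participant. Those ranks always sum to k(k+1)/2. With the seven visits listed in the Abstract (baseline, days 5 and 10, four follow-ups) the sum is 7 × 8 / 2 = 28, a mean rank of 4 for every participant in either arm. The difference between arms in mean rank is therefore zero by construction. The Intervention section counts three follow-ups; with k = 6 the sum is 21 and the mean 3.5, and the conclusion is the same.

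**2. What baseline can carry.** A person who cannot complete a test cannot score 3 on it. Scores of 1 (attempted) or 2 (partially recovered) remain possible. I read 0 as the bottom of the scale, although the article labels it as complete. The baseline is restricted in range, not constant.

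**3. The plan's own sample size.** Evaluable: 34 × 0.88 = 29.9, about 30, or 15 per arm. Read 0.84 as Cohen's d, so f = 0.84 / 2 = 0.42. For a between-group factor over m time points, λ = N f² m / (1 + (m − 1)ρ). With N = 30, ρ = 0.4 and m = 3 (three time points are stated for Aim 2 and assumed here), λ = 30 × 0.1764 × 3 / 1.8 = 8.82 and power is 81.8%. Then 30 / 0.88 = 34.1, which reproduces N = 34. The printed f = 0.6 does not lead to 34: at one time point it needs 24 evaluable, or 28 with attrition.

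**4. Gain from a covariate, one time point, normal scale.** Two-sided α = 0.05 ("Statistical significance corresponds to a p-value less than 0.05"; sidedness is not stated). Unadjusted λ = N(d/2)² on 28 df. Adjusted for a covariate with correlation r to the outcome, λ / (1 − r²) on 27 df. For d = 0.84, λ = 30 × 0.1764 = 5.29. For f = 0.6 (d = 1.2), λ = 30 × 0.36 = 10.8.

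| r | λ, d = 0.84 | Power, d = 0.84 | Gain | Power, f = 0.6 | Gain |
|---|---|---|---|---|---|
| none | 5.29 | 60.3% | – | 88.7% | – |
| 0.2 | 5.51 | 61.9% | 1.6 | 89.8% | 1.1 |
| 0.3 | 5.82 | 64.3% | 4.0 | 91.3% | 2.6 |
| 0.4 | 6.30 | 67.7% | 7.4 | 93.3% | 4.6 |
| 0.5 | 7.06 | 72.6% | 12.3 | 95.5% | 6.8 |

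**5. Three-time-point version.** The variance of the mean is 1.8 / 3 = 0.6, reduced to 0.6 − r². Power goes from 81.8% to 84.2%, 87.4%, 91.7% and 96.3% at r = 0.2, 0.3, 0.4 and 0.5.

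**6. Ordinal outcome.** Simulation of a 0-3 score, 15 per arm, d = 0.84 on the latent scale, 4,000 runs per setting, rank ANCOVA against the unadjusted comparison:

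| Controls scoring 0 | r = 0.4 | r = 0.5 |
|---|---|---|
| spread over the scale | 54.3% → 58.7% | 55.0% → 63.1% |
| 50% | 52.0% → 56.5% | 52.6% → 60.7% |
| 70% | 50.1% → 52.8% | 49.4% → 55.0% |
| 85% | 38.9% → 40.6% | 40.2% → 43.9% |

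The gains run from about 2 to about 8 points and are smallest where most controls stay at 0.

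**The case against.** **This is a condensed article, and covariates are commonly left to the analysis plan.** That would dispose of a complaint about silence. Here the article names a specific test and its only factors, and that test cannot compare the arms or take a covariate. The choice is stated and open to criticism.

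**The Friedman label may be loose.** The authors may intend a rank-transformed two-way ANOVA, which would have a between-arm term. The sample-size text does suggest that a between-arm comparison is meant. In that case the wording still has to change, and a covariate can be added in the same edit.

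**An unadjusted randomised comparison is valid.** This stands. Chance imbalance in strength is covered by the significance level, so the argument for adjustment is precision and not bias.

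**The power figures are not those of the planned test.** This also stands. They describe between-arm comparisons that could replace it. For the same reason one should not say that the spread in strength inflates the Friedman error term, because ranking within participants removes differences in level.

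**The biological support is thin.** The tissue-sparing statement concerns rats, and the article goes on to say that very little sparing (under 2%) can suffice for meaningful gains. It makes strength a plausible predictor and no more.

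**Conclusion.** The point holds as a mismatch between method and question, together with an inexpensive improvement. The Aim 1 test as written does not properly compare AIH with SHAM and cannot use baseline strength. Adjustment raises power in every variant examined, but its size is uncertain: about 2 to 12 points from about 60% at d = 0.84 for r = 0.2 to 0.5, about 1 to 7 at f = 0.6, and about 2 to 8 for a simulated 0-3 score at r = 0.4 to 0.5. The three-time-point version gains more (about 2 to 15), but from a starting power already above 0.8. All of this assumes two-sided testing, 15 evaluable per arm and 0.84 read as Cohen's d.

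A reader might infer more than the article supports:

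- **That 7 to 12 points of power are lost.** This needs r = 0.4 to 0.5, and the article gives no strength-outcome correlation. Its ρ = 0.4 belongs to the repeated-measures sample-size calculation and says nothing about strength.
- **That the baseline score is at floor by design.** Only a score of 3 is excluded.
- **That Aim 1 is the smallest comparison.** It is the smaller aim, but with balanced arms 34 / 2 = 17 per arm, the same as 51 / 3 = 17 in Aim 2.
- **That baseline LEMS is certainly available.** An improved LEMS implies an earlier value, but the text on screening says only strength, and the assessment schedule (Table 3) is not visible here.

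**What to change.** Replace the Friedman analysis under Hypothesis 1 with a between-arm comparison of AIH and SHAM on the recovery score at one stated time point. Use either a rank ANCOVA (Quade) or a proportional-odds model, with baseline strength as the single pre-specified covariate (LEMS, if it is recorded at baseline). Keep the unadjusted between-arm comparison as a sensitivity analysis. Fix the covariate and the time point before unblinding, so that neither can be chosen on the results. In the same edit, reconcile the Aim 1 power inputs (0.84, f = 0.6 and F with 1 and 39 df) with the analysis adopted.

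The cost is analysis wording and about one degree of freedom. No further participants are needed, and no new data if strength is recorded at baseline in usable form.

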### Hypothesis and aims

The fundamental hypothesis guiding this study is that repetitive exposure to AIH (10 sessions in 2 weeks) will enhance walking recovery in ambulatory and non-ambulatory persons with subacute SCI, presumably by augmenting neural plasticity through a combination of spontaneous neural recovery and AIH-mediated spinal mechanisms. To test this hypothesis, we are carrying out three specific aims: 1) to quantify the impact of daily AIH (alone) on restoring walking ability in persons with subacute SCI who are initially unable to walk overground, 2) to quantify the beneficial effects of daily AIH with walking practice (daily AIH + WALK) on improving walking ability in persons with subacute SCI who are initially able to walk overground and 3) to determine if the benefits of daily AIH in persons with subacute SCI are without evidence of maladaptive changes and pathology (e.g. hypertension, autonomic dysreflexia, pain, and spasticity) [10, 23].

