**Table 1 Tab1:**
[figure not shown]
Study eligibility criteria

Since we do not yet know of any differences in responsiveness to daily AIH according to the gender or race of persons with SCI [27], we will balance our recruitment across testing groups (Aims 1 and 2) based on age, gender, and race. However, to protect against possible side effects of daily AIH, women who are pregnant or nursing a child may not take part in this study, as the effects of daily AIH on the developing fetus or infant have not been studied.
B.Informed consent process

Potential participants must read and sign the study’s consent form and Health Insurance Portability and Accountability Act (HIPAA) waiver prior to study enrollment. Our consent form incorporates the International Campaign for Cures of Spinal Cord Injury Paralysis inclusion and exclusion criteria recommendations to account for ethical considerations, safety, and potential confounds during participant recruitment [28]. Potential participants who sign the consent form undergo a medical screen by one of the study physicians and a physical screen by one of the study physical therapists. The medical screen ensures the participant meets all inclusion criteria and has no underlying medical conditions that may make them ineligible to participate. During the physical screen, the team physical therapist evaluates the individual’s functional walking ability, strength, spasticity, and pain levels using standardized clinical assessments that have high inter-rater reliability.

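### The Aim 2 model does not pre-specify time since injury, a plausibly prognostic value known for everyone, so precision may be lost and the result is left open to an unlucky draw

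*Protocol article*

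**What the plan says.** Under Statistical analysis, Hypothesis 2, the article gives the model for TUG, 10MWT and 6MWT: "We will use intervention (daily AIH + WALK, daily SHAM+WALK, WALK) and time (day) as the fixed main effects, with subject as random effect". Differences from baseline are then compared at mid-test, post-test and follow-ups, with Tukey-Kramer for pairwise differences. One form of adjustment is foreseen: "If baseline measures are significantly different between intervention groups, we plan to use an analysis of co-variance (ANCOVA) to analyze these data". Which baseline measures are meant is not said.

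At the design stage, Randomization and stratification says: "We stratify eligible participants into either an ambulatory or a non-ambulatory group based on their initial walking function". Study recruitment and selection adds that "we will balance our recruitment across testing groups (Aims 1 and 2) based on age, gender, and race". Neither mentions time since injury.

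The rationale bears on that variable. The Background states: "Spinal plasticity peaks within the first year after injury and thus, offers a window of opportunity for early AIH treatments". Hypothesis and aims explains the expected benefit as arising "presumably by augmenting neural plasticity through a combination of spontaneous neural recovery and AIH-mediated spinal mechanisms". The Discussion presents the one-year follow-up as a way to study a full year of recovery in the subacute stage. Entry is open to people less than 12 months after injury (Abstract).

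**The concern.** A participant enrolled one month after injury and another enrolled at eleven months may be at different points of spontaneous recovery. If so, part of the spread in walking change comes from when they entered, not from what they received. A model without that variable leaves this spread in the error term. With about 15 completers per arm, the arms may also differ in time since injury by chance, and the contrast then carries some of that difference.

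The value is fixed before randomization and must be known to establish that a participant is within the subacute window. Two things are at stake: the precision of the Aim 2 contrasts, and how convincing one realized result is if the arms turn out unequal on this variable.

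**Working it through.** **Inputs.** From Sample size, Aim 2: difference in 6MWT change about 100 m, pooled SD 90 m, N = 51 including 12% attrition, α = 0.05, power above 0.8. Assumed: equal allocation, a two-sided test, and 90 m as the SD of the change being compared. The correlation r between (log) time since injury and 6MWT change is not in the document; r = 0.1, 0.3 and 0.5 are shown.

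**The plan's own figure.** 51 / 3 = 17 per arm, and 17 × 0.88 = 14.96, so about 15 completers per arm. (3 × 15 × 1.12 = 50.4, rounded up, gives 51.) The standard error of a pairwise contrast is 90 × √(2/15) = 32.9 m, and the noncentrality is 100 / 32.9 = 3.04. With error from three arms (42 df):

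- one pairwise test, critical value 2.018: power 0.84, so the stated target is met;
- Tukey-Kramer over three arms, critical value 3.436 / √2 = 2.429: power 0.73.

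**With the covariate.** Residual SD = 90 × √(1 − r²), with one degree of freedom fewer (41):

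| r | Residual SD (m) | SE (m) | Power, one pair | Power, Tukey-Kramer |
|---|---|---|---|---|
| none | 90.0 | 32.9 | 0.84 | 0.73 |
| 0.1 | 89.5 | 32.7 | 0.85 | 0.73 |
| 0.3 | 85.9 | 31.3 | 0.88 | 0.77 |
| 0.5 | 77.9 | 28.5 | 0.93 | 0.86 |

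These figures ignore the small loss from estimating the slope under imbalance. A two-arm simulation that includes it gave 0.836 unadjusted and 0.838 adjusted at r² = 0.05, and 0.835 and 0.896 at r² = 0.20.

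**Chance imbalance.** The difference between two arms in mean time since injury, in SD units, has standard deviation √(2/15) = 0.365. An imbalance above 0.5 SD therefore has probability P(|Z| > 0.5/0.365) = 0.17 for one pair. By simulation it is 0.29 for AIH+WALK against at least one comparator. A 0.5 SD imbalance moves the 6MWT contrast by r × 0.5 × 90, which is 4.5, 13.5 and 22.5 m at r = 0.1, 0.3 and 0.5.

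This is not error on top of the standard error. At r = 0.5 the unadjusted variance 90² × 2/15 = 1080 splits into 270 from the covariate (an SD of 16.4 m) and 810 from the rest. Simulated type I error of the unadjusted test is 5% over all randomizations. Among draws with imbalance above 0.5 SD it is 6.5%, 7.4%, 10.3% and 12.9% at r² = 0.05, 0.10, 0.20 and 0.30. Adjustment brings it back to about 5%.

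**The existing safeguard.** A two-sample test at 15 per arm (28 df, critical value 2.048) is significant only when the difference exceeds 2.048 × 0.365 = 0.75 SD. Smaller imbalances would pass unadjusted even if the clause covered time since injury.

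**Form of the adjustment.** If raw scores including baseline are the response, a covariate term βx has the same value at every visit of one person and cancels from the change between baseline and visit t. A simulated complete data set confirmed this: the main effect alone left the arm-by-visit estimate and its standard error unchanged to rounding. A visit-specific slope leaves (γ_t − γ_0)x in the change and does adjust it.

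**The case against.** Several points on the other side stand. The unadjusted randomized comparison is unbiased, and planned power is met for one pairwise test without any covariate. The correlation has no source in the document, and at r = 0.1 the gain is negligible. The planned sizing uses three time points; if these are baseline, mid-test and post-test, they span two weeks, when recovery linked to time since injury may matter less than over a year. The eligibility table is not shown, so the spread of entry times is not fully known. An analysis plan that is not shown may add covariates. However, the article writes out the model and an adjustment rule, and that rule is data-dependent.

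Four stronger readings are tempting and not supported:

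- A reader might infer that the protocol itself treats time since injury as the driver of recovery. It says that plasticity peaks within the first year and counts spontaneous recovery in a presumed mechanism. Every participant is inside that year, and no gradient within it is stated.
- A reader might infer that omitting the term biases the trial or inflates false positives. Overall type I error is 5%; the excess exists only conditional on an unlucky draw.
- A reader might set the imbalance shift against the 23.9 m gain with AIH alone in Sample size. That is a preliminary within-treatment change; the planned Aim 2 contrast is about 100 m.
- A reader might extend the change to Aim 1. The planned analysis there is rank-based, so adjusting it would replace the method, which this point does not justify.

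**Conclusion.** The point holds as one of efficiency and robustness, not of validity. The stated Aim 2 model omits a baseline value that is known for everyone and plausibly prognostic on the protocol's own rationale. Allocation is not stratified on it, and the significance-triggered ANCOVA is a weak substitute.

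The size is uncertain. At the planned 100 m, adjustment adds between almost nothing (r = 0.1) and about 0.09 (r = 0.5) to the power of one pairwise test. Under the planned Tukey-Kramer comparison, where unadjusted power is 0.73, the gain ranges from almost nothing to about 0.13. The shortfall under Tukey-Kramer comes from the multiplicity adjustment, not from the missing covariate; adjustment would offset it only if r is fairly large. All figures assume equal allocation, 15 completers per arm and 90 m as the SD of change.

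**What to change.** Pre-specify log time since injury at enrolment as a covariate in the Aim 2 analysis of all three outcomes, to be used whatever the observed balance, and make that adjusted analysis the primary one. State which response is modelled, because this decides how the covariate must enter:

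- change from baseline as the response: add the covariate as a term;
- raw scores including baseline as the response: add the covariate with its interaction with visit, since a main effect alone does nothing for the contrast of interest.

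Do not make this adjustment depend on a baseline significance test. Leave Aim 1 as it is on this point.

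The cost is one degree of freedom in the first form, or one per post-baseline visit in the second, and no new data. If the covariate proves weak, almost nothing is lost.

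### Aim 2 adjusts for baseline only if a baseline significance test is positive, which forgoes power, and its main-effects model cannot give the visit-by-visit arm differences it promises

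*Protocol article*

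**What the plan says.** All of this is in the Protocol article. Under Statistical analysis, Hypothesis 2, the TUG, 10MWT and 6MWT scores are repeated measures in a linear mixed model. Its terms are intervention (three arms) "and time (day) as the fixed main effects, with subject as random effect". The next sentence sets the comparison: "Differences from baseline scores will be compared between and within interventions at mid-test, post-test, and follow-ups". The section then adds the rule for baseline: "If baseline measures are significantly different between intervention groups, we plan to use an analysis of co-variance (ANCOVA) to analyze these data". The significance rule for all hypotheses is: "Statistical significance corresponds to a p-value less than 0.05".

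The Sample size section gives the planning figures for Aim 2: "we anticipate the difference in change of walking distance between daily AIH + WALK vs daily SHAM+WALK or vs WALK will be approximately 100 m", "using a pooled standard deviation of 90 m", a correlation of 0.4, alpha .05, power above 0.8, three time points, and N = 51 including 12% attrition. It does not say whether 90 m is the SD of a 6MWT score or of its change, nor that 0.4 is specifically the correlation between baseline and follow-up. Under Randomization and stratification, allocation within the ambulatory group follows a balanced scheme generated in advance.

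**The concern.** Two separate matters arise.

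**The baseline rule.** When arms are randomised, a significant baseline difference is a chance finding. The reason to adjust is that baseline predicts the outcome, and this holds whether or not the arms happen to differ. A rule triggered by the test therefore picks the model from the data, leaves most trials unadjusted, and gives up power that could be had from a measurement already taken. With about 15 completers per arm, that is a real cost.

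**The model terms.** A model with only main effects of intervention and time forces the arm difference to be the same at every visit. The plan wants arm differences in change at mid-test, at post-test and at each follow-up. The stated model has no term that lets those differ. The text also leaves open whether the response is the raw score with baseline included or the change from baseline, and that choice decides what the intervention coefficient means.

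**Working it through.** **Inputs.** Difference 100 m, SD 90 m, correlation ρ = 0.4, alpha .05, N = 51 with 12% attrition (Sample size). Assumed: two-sided test, 1:1:1 allocation, ρ as the baseline-to-follow-up correlation, compound symmetry. Completers: 51 × 0.88 = 44.9, so about 15 per arm.

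**The plan's own figure.** For 100 m and 90 m, the normal approximation gives 2 × (1.96 + 0.84)² × 0.9² = 12.7, so 13 per arm: 39, or 45 after dividing by 0.88. The t-test gives 14 per arm: 42, or 48. N = 51 is not reproduced, but nothing below depends on that. The claim of power above 0.8 is met if 90 m is the SD of change: 15 per arm give 83.6%.

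**Step 1: variance at one post-baseline visit**, in units of the score variance.
- Change score: 2(1 − ρ) = 1.20.
- ANCOVA: 1 − ρ² = 0.84.
- Ratio: (1 + ρ)/2 = 0.70 at ρ = 0.4, 0.80 at 0.6 and 0.90 at 0.8.

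**Step 2: power at 100 m, 15 per arm.** Two-sample noncentral t, noncentrality (100/SD) × √(15/2).

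| Reading of 90 m | ρ | SD change | SD ANCOVA | Power change | Power ANCOVA |
|---|---|---|---|---|---|
| SD of change | 0.4 | 90.0 | 75.3 | 0.836 | 0.939 |
| SD of a score | 0.4 | 98.6 | 82.5 | 0.765 | 0.893 |
| SD of change | 0.8 | 90.0 | 85.4 | 0.836 | 0.872 |
| SD of a score | 0.8 | 56.9 | 54.0 | 0.996 | 0.998 |

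**Step 3: the two-step rule.** The baseline test is positive in about 5% of trials, so power is roughly 0.95 × change + 0.05 × ANCOVA.
- SD of change, ρ = 0.4: 0.95 × 0.836 + 0.05 × 0.939 = 0.841.
- SD of a score, ρ = 0.4: 0.95 × 0.765 + 0.05 × 0.893 = 0.771.

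Simulation agrees. Rule versus always-ANCOVA is about 0.84 versus 0.93 (SD of change), 0.77 versus 0.88 (SD of a score), and 0.83 versus 0.86 at ρ = 0.8 with change SD 90 m. Pooling the residual variance over all three arms moves these by about 0.01; for example, the second pair becomes 0.78 versus 0.90. Simulated type I error of the rule was 4.5% at ρ = 0.4.

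**Step 4: what the intervention main effect estimates**, assuming a constant effect after baseline.
- If change is the response, it is the visit-averaged difference in change, undiluted.
- If raw scores including baseline are the response, it is p/(p + 1) of the effect, where p is the number of post-baseline visits. With p = 2 (three time points, as in Sample size) this is 2/3, or 66.7 m of 100 m. With p = 6 (the visits listed in the Abstract) it is 6/7, or 85.7 m.
- The power cost on the raw-score reading varies. With score SD 90 m and ρ = 0.4, p = 2 gives 0.715, against 0.872 for averaged change and 0.979 for ANCOVA. With p = 6 it gives 0.951, against 0.939 and 0.999.
- On either reading, one intervention coefficient cannot give a separate arm difference at each visit.

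**The case against.** Several points can be made for the plan, and some of them stand.

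- **The planned power may survive.** It does if 90 m is the SD of change: the rule gives about 0.84 at 100 m. A reader might infer that the plan misses its target, but this happens only if 90 m is the SD of a score and ρ is near 0.4.
- **The correlation may be higher than 0.4.** The Outcome measures section describes these tests as highly reliable, so this is plausible. At 0.8 the gain is small, and it vanishes if 90 m is also the SD of a score. This stands and bounds the size of the point.
- **A data-chosen model suggests false positives.** A reader might infer that type I error is inflated. The simulation does not support this.
- **The model seems to have no term for differential change.** A reader might take the dilution to 2/3 as a fact about the plan. It follows only if raw scores with baseline are the response. The sentence on differences from baseline supports the other reading, and comparing ANCOVA with an unadjusted change score presupposes that other reading. The two losses therefore should not be added together.
- **Labelling time by day could suggest a straight line to 12 months.** The text specifies no slope, and it lists discrete visits.
- **An article may shorten a model statement.** This is fair, and the full protocol may contain the interaction. But the article does more than stay silent: it names the fixed effects as main effects and then promises comparisons they cannot supply.
- **Planned precision is being lost.** This would be too strong, because the sample size was not built on ANCOVA. The gain forgone is an available one.

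**Conclusion.** The point holds as a should-fix. The conditional rule is stated outright and is inefficient: it behaves almost exactly like an unadjusted change score. At the plan's own ρ = 0.4 and 100 m it costs roughly 0.09 to 0.11 in power (0.84 versus 0.93, or 0.77 versus 0.88). At ρ = 0.8 with change SD 90 m it costs about 0.03. These sizes rest on 15 completers per arm, one post-baseline visit, two-sided alpha .05, and 0.4 being the baseline-to-follow-up correlation. Error control is not at issue.

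The mismatch between a main-effects model and visit-specific arm comparisons also holds, whichever response is meant. The documents do not support anything stronger about dilution of the treatment coefficient, because they do not settle whether the response is the raw score or the change.

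**What to change.** In Statistical analysis, Hypothesis 2:

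1. Delete the sentence that makes ANCOVA conditional, and carry out no significance tests of baseline between arms.
2. State the model for each of TUG, 10MWT and 6MWT. The response is the post-baseline scores. The fixed effects are the baseline value (always), intervention, visit as a category, and intervention by visit. Keep a participant-level random effect.
3. Report the contrasts of AIH+WALK with SHAM+WALK and of AIH+WALK with WALK at a named visit.
4. In Sample size, say whether 90 m is the SD of a score or of change, and what the correlation of 0.4 refers to.

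This changes wording only. Baseline is already measured, so no participants, visits or procedures are added. The change should be made before any unblinded analysis.
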